### Depression

Depression will be assessed by using the Patient Health Questionnaire-9 (PHQ-9). The PHQ-9 is widely used in patients with chronic diseases, including diabetes [8]. On the basis of a previous study [11], we operationally define participants with PHQ-9 scores ≥ 10 as having depressive symptoms. The reliability and validity of the Japanese version of PHQ-9 have been established [19]. In this study, we define depression as having clinical diagnosis (DSM-5, American Psychiatric Association) [20] or having both severe depressive symptoms and receiving antidepressant.

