## Background

Prevention, or slowing the progression, of diabetic nephropathy is one of the important goals in diabetes care [1, 2]. As the kidney disease progresses, end-stage renal disease (ESRD) occurs and requires either dialysis or transplantation, which places significant burden on the patient and the society. Diabetes is one of the predictors of a poor perceived quality of life in patients with ESRD [3], and the prevalence of diabetes could impose an increasing economic burden due to substantial costs for patients with ESRD [4].

Depression is observed in approximately 20 % of patients with diabetes [5, 6]. Although adherence to hypoglycemic medication is important for the prevention and management of diabetic nephropathy [2], a meta-analysis indicates that depression is associated with lower adherence to hypoglycemic medication in patients with diabetes [7]. Furthermore, depression also adversely affects adherence to other key medications for hypertension and hyperlipidemia - the main risk factors of diabetic nephropathy [8]. Considering the high prevalence of depression and that depression is rather commonly undiagnosed in patients with diabetes [9], the impact of depression on diabetic nephropathy is a growing concern.

The literature has reported the morbidity and mortality of kidney disease in patients with depression. A recent meta-analysis showed that depression was observed in 21.4 % of patients in chronic kidney disease (CKD) stage 1–5 [10]. Comorbid patients with diabetes and depression had higher risks of microalbuminuria [11] and ESRD than those without depression [12]. Patients with diabetic nephropathy who have had a depressive episode were more likely undergo dialysis than those without a depressive episode [13], and the mortality was 1.5-fold higher in diabetes patients with depression than in those without depression [14, 15].

In patients with type 2 diabetes, we aim to examine (1) depression as a predictor of renal function decline, and (2) how adherence to hypoglycemic medication relates to depression and renal function decline.

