### Sample-size calculations

We calculated sample size as 550 patients (165 for the depression group and 385 for the non-depression group) having (1) a 30 % prevalence of depression, (2) 10 % difference in microalbuminuria rate (18 % in the depression group and 8 % in the non-depression group), and (3) an 88 % chance of detecting a true difference in microalbuminuria at the 5 % level of significance. Calculation was based on the chi-square test with continuity correction and we did not take into account of adherence since it might be an intermediate variable. The prevalence of depression in patients with diabetes was 20 % in previous studies [5, 6, 10, 11]; however, we estimated 30 % owing to the inclusion of patients from psychiatric clinics in our study. The prevalence of microalbuminuria was estimated by using the data of the Japanese Society of Nephrology [18] and those from a previous study [11].

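### As written, the depression definition leaves patients with PHQ-9 ≥ 10 who have neither a diagnosis nor an antidepressant in the non-depressed reference groups, and it gives no cut-off for severe symptoms.

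*Protocol article*

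**What the plan says.** The Depression section of the protocol article opens with "Depression will be assessed by using the Patient Health Questionnaire-9 (PHQ-9"). The abstract also gives the Patient Health Questionnaire as the depression measure, and PHQ-9 is the only entry under depression in Table 1.

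The same section sets a threshold: "On the basis of a previous study [11], we operationally define participants with PHQ-9 scores ≥ 10 as having depressive symptoms". It then gives a different rule for depression itself: a DSM-5 clinical diagnosis, "or having both severe depressive symptoms and receiving antidepressant". It does not say which PHQ-9 score counts as severe, or whether the threshold of 10 plays any part in the rule.

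Study endpoints and Data analysis both use four groups formed by depression (+/−) and adherence (+/−), so every patient must be placed on one side. The Background states that "depression is rather commonly undiagnosed in patients with diabetes".

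Sample-size calculations assume "550 patients (165 for the depression group and 385 for the non-depression group"), with microalbuminuria in "18 % in the depression group and 8 % in the non-depression group". On the source of the rates it says: "The prevalence of microalbuminuria was estimated by using the data of the Japanese Society of Nephrology [18] and those from a previous study [11"].

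**The concern.** Being depression-positive requires recognition or treatment: either a clinician has made the diagnosis, or the patient has severe symptoms and takes an antidepressant. A patient who scores 10 or more on PHQ-9 but has neither meets no branch of the rule. With only two depression categories, that patient joins the reference side, and this would be so even at the maximum score.

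If these patients have a higher renal risk than patients without depressive symptoms, as the study's own hypothesis suggests, the reference rate rises and the depression odds ratio moves toward 1. The first study aim, depression as a predictor, and the four-group comparison both depend on this contrast.

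Two further problems follow. Without a cut-off for severe, two sites could apply the second branch differently. And the assumed rates draw partly on the study that the article credits for the threshold of 10, so they may describe an exposure other than the one to be analysed.

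**Working it through.** **Classification from the text**

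| Baseline patient | Diagnosis | Severe symptoms and antidepressant | Group as written |
|---|---|---|---|
| Diagnosed, any PHQ-9 | yes | either | depression + |
| No diagnosis, severe, on antidepressant | no | yes (cut-off not stated) | depression + |
| No diagnosis, PHQ-9 ≥ 10, no antidepressant | no | no | depression − |
| No diagnosis, PHQ-9 ≥ 10 but below severe, on antidepressant | no | no | depression − |
| No diagnosis, PHQ-9 < 10 | no | no | depression − |

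The article describes no third category, exclusion or sensitivity analysis for rows three and four.

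**Reproducing the plan's figure**

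Inputs from Sample-size calculations: n₁ = 165, n₀ = 385, p₁ = 0.18, p₀ = 0.08, 5 % level, chi-square test with continuity correction. The article does not state sidedness; two-sided reproduces its figure.

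Normal approximation: power = Φ{[d − ½(1/n₁ + 1/n₀) − 1.96·s₀]/s₁}, where d = p₁ − p₀, s₀ is the pooled standard error and s₁ the unpooled one.

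- d = 0.10; correction ½(1/165 + 1/385) = 0.00433
- pooled rate (165 × 0.18 + 385 × 0.08)/550 = 0.11; s₀ = 0.0291; s₁ = 0.0330
- (0.10 − 0.00433 − 1.96 × 0.0291)/0.0330 ≈ 1.17, so power = 0.879, against the stated 88 %

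The matching sample-size formula gives 553 patients against the stated 550. Exact power, summing the binomial probabilities of all tables in which the corrected chi-square is significant, is 0.886. The calculation is right for a clean 18 % versus 8 % contrast.

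**Effect of affected patients in the reference group**

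Let c be the share of the reference group with PHQ-9 ≥ 10 who miss the definition, and r their microalbuminuria risk. Neither is in the documents; both are assumptions. Then p₀ = 0.08(1 − c) + r·c. The exposed rate is held at 0.18 and the groups at 165 and 385. The odds ratio is (0.18/0.82)/[p₀/(1 − p₀)].

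| c | r | p₀ | Odds ratio | Power, approximate | Power, exact |
|---|---|---|---|---|---|
| 0 | – | 0.080 | 2.52 | 0.879 | 0.886 |
| 10 % | 13 % | 0.085 | 2.36 | 0.839 | 0.844 |
| 10 % | 18 % | 0.090 | 2.22 | 0.792 | 0.795 |
| 20 % | 18 % | 0.100 | 1.98 | 0.678 | 0.680 |

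**Letting the exposed rate rise**

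A narrower case group may have a rate above 18 %. At 19.5 % versus 9 %, exact power is 0.892; at 21 % versus 10 %, it is 0.900. These exposed rates are also assumptions, but they show that the loss is not inevitable.

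**Cost of a third category**

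At c = 20 %, removing the affected patients leaves 385 × 0.8 = 308 in the reference group at 8 %. The correction is ½(1/165 + 1/308) = 0.0047, the pooled rate (29.7 + 24.64)/473 = 0.115, s₀ = 0.0308 and s₁ = 0.0337. Then (0.10 − 0.0047 − 1.96 × 0.0308)/0.0337 ≈ 1.04, so power is about 0.85 by the same approximation. Leaving them in gives 0.678.

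**The case against.** A clinical diagnosis is a defensible exposure and more specific than a questionnaire threshold. That stands: nothing requires the sponsor to give up the clinical definition as primary. A reader might infer that the exposure should be the union of PHQ-9 ≥ 10, diagnosis and antidepressant use. That union would bring screen-positive non-cases into the exposed group, which can also dilute the contrast. The documents show no net gain from it.

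A reader might also infer that the study has about 68 % or 80 % power instead of 88 %. The documents do not support this. They give neither the share affected nor its risk, and a higher exposed rate could restore the power.

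The Background remark on missed diagnoses concerns patients with diabetes in general. Here 14 of the 20 clinics come from a psychiatric care network, where missed depression is plausibly rarer. The article also does not say whether the DSM-5 diagnosis is taken from the chart or made during the study; assessing every participant would shrink the affected group. Both points may limit the size of the problem. However, the article describes no such assessment, and Table 1 lists only PHQ-9.

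Finally, the mismatch with the sample-size rates cannot be proved. Reference 11 is not available here, and the rates also draw on national nephrology society data (reference 18). To say that the assumed effect belongs to a different exposure would go too far.

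A condensed article may leave a cut-off to the full protocol. But this article prints the definition that forms the groups, and as printed it sets a PHQ-9 threshold without giving it a role.

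**Conclusion.** The point holds as a defect in the stated exposure definition. By its wording, patients with PHQ-9 ≥ 10 who have no diagnosis and no antidepressant are in the reference groups, and nothing else in the article changes that. The word severe has no cut-off, so the second branch cannot be applied uniformly.

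Bias toward the null is conditional: it occurs if these patients have a higher risk than the rest of the reference group. Its size is unknown. The illustrative exact power of 0.84, 0.80 and 0.68 rests on assumed shares of 10 % to 20 %, assumed risks of 13 % to 18 %, and an exposed rate fixed at 18 %. It concerns the unadjusted microalbuminuria comparison used for sample size. A net loss of power is possible but not established.

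That the 18 % and 8 % rates may not fit the exposure analysed is an inference from the article's citing reference 11 for both the threshold and, in part, the rates. The sponsor should settle it.

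**What to change.** 1. Keep the clinical definition as primary if preferred, and state the PHQ-9 score that counts as severe.
2. Place patients with baseline PHQ-9 ≥ 10 who do not meet the definition in a separate third category, outside the reference groups, and report their results.
3. Prespecify a sensitivity analysis with baseline PHQ-9 ≥ 10 or a clinical diagnosis as the exposure.
4. State whether the 18 % and 8 % rates apply to the chosen definition, and re-justify them if they do not.

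PHQ-9 is already planned for baseline, so no new data are needed. The cost is wording, one extra analysis and a somewhat smaller reference group.

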### Medication adherence

Medication adherence will be assessed by using the medication possession ratio (MPR). The MPR is defined as the ratio of the number of days prescribed per 365 days based on medical records. The MPR is used as an indicator for adherence improvement programs [21, 22]. In this study, we operationally define low adherence as < 80 % because a previous study reported that the mean adherence ranged between 78 % and 82 % [23]. Medication adherence will also be assessed by using the Japanese version of the Morisky Medication Adherence Scores (MMAS-8). MMAS-8 is an eight-item self-reporting measure of medication-taking behavior [24, 25]. The first seven items have a dichotomous response (yes or no); the eighth item has a five-point Likert scale response. The total score of MMAS-8 ranges from 0 to 8. A higher score represents a higher adherence to medication. In addition, a single-question Oral Hypoglycemic Agent (OHA) adherence scale will be used specifically to assess adherence to hypoglycemic medication [23]. The question is, “On average, how would you rate your ability to take all your diabetes medications as your doctor prescribed?,” answered with a five-point Likert scale (very poor, poor, fair, good, very good, and excellent).

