### Participants

All patients who meet inclusion criteria during the study period will be invited to participate in the study. Participants will be eligible for the study if they (1) are 20 years and older, (2) outpatients with type 2 diabetes receiving hypoglycemic medications, and (3) can complete a questionnaire in Japanese. Patients will be excluded if they (1) have cognitive impairment, (2) are pregnant, and (3) have severe disease of the adrenal glands, liver dysfunction, or severe renal impairment (serum creatinine ≥ 2.0 mg/dL).

Eligible patients will be approached by physicians at each site. After an explanation of the study, written informed consent will be obtained from each patient. Patients will be able to access research staff members who are not in charge of their treatment to withdraw from the study at any time.

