### Study endpoints

The primary outcome is the decline of renal function in four subtypes categorized according to depression and adherence (depression/adherence: +/−, +/+, −/+, −/−) at 12 months. The secondary outcomes include clinical variables, quality of life, and attitude of physicians toward depression. We assess physician attitudes to depression to confirm no effects of the attitudes on primary outcome in a sensitivity analysis. Previous systematic review suggests necessity for cohort studies to examine information on patients with multimorbidity across all ages and socioeconomic groups [16]. Although analyses of secondary outcomes will be underpowered, we include the analyses in the protocol for confirmation of the analysis of primary outcome and implication for the future studies.

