### Data analysis

We will use multivariable linear regression analysis to evaluate the effects of medication adherence of comorbid patients with type 2 diabetes and depression on the decline of renal function. We will consider other potential confounding factors including smoking, hypertension, hyperlipidemia, and HbA1c. The risk of decline of renal function will be estimated for four groups by adherence (+/−) and depression (+/−) by odds ratio and 95 % confidence interval.

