## Discussion

To our knowledge, the present study will be the first study to examine how adherence to hypoglycemic medication relates to the decline of renal function in comorbid patients with type 2 diabetes and depression. Given the prevalence of diabetes and depression, the impact of the comorbidity of these diseases is increasingly important. We will use all standardized measures. Renal function is assessed by urinary ACR and eGFR. As an increase of ACR is observed earlier than a decrease of eGFR in CKD, our study design aids in the better understanding of renal function decline from the early phase in comorbid patients with type 2 diabetes and depression. Adherence is assessed by both objective (MPR) and subjective (MMAS-8 and OHA) measures. MMAS-8 measures general adherence to medication, whereas OHA specifically measures adherence to hypoglycemic medication. A wide range of outcomes, including clinical variables, quality of life, and attitude of professionals toward depression, are also assessed.

This study design has several limitations. First, the participants will be patients who regularly visit clinic, causing a risk of bias. This might limit the generalizability of the findings. Second, our study will not include all possible confounding factors related to diabetes, depression, hypoglycemic medication adherence, and decline of renal function; nevertheless, we plan to control the major potential confounding factors.

The results of the present study will have implications to practitioners in diabetes care, policy makers, and researchers for screening a group of patients at a high risk for diabetic nephropathy (i.e., comorbid patients with type 2 diabetes and depression plus poor adherence to hypoglycemic medication) and for the development of intervention strategies for the prevention and treatment of diabetic nephropathy.

In conclusion, the results of this protocol study will indicate the importance of depression in diabetic care through exploring (1) depression as a predictor of renal function decline, and (2) how adherence to hypoglycemic medication relates to depression and renal function decline. Our research will provide insights to all clinicians who encounter comorbid patients with diabetes and depression in dairy practice.

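### Grouping by days prescribed in a cohort of regular attenders is likely to class prescribed non-takers as adherent and dilute the adherence contrast

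*Protocol article*

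**What the plan says.** Under Medication adherence, the protocol article builds MPR from prescribing records: "The MPR is defined as the ratio of the number of days prescribed per 365 days based on medical records". The cut-off and its justification follow: "we operationally define low adherence as < 80 % because a previous study reported that the mean adherence ranged between 78 % and 82" (per cent). No other adherence cut-off appears in the article.

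Two self-report measures are also collected at baseline and 12 months: the MMAS-8, which the Discussion describes as covering medication in general, and a single Oral Hypoglycemic Agent (OHA) item, specific to hypoglycemic drugs. Neither has a cut-off or a stated role in forming groups.

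Adherence status enters the main comparison directly. Study endpoints: "The primary outcome is the decline of renal function in four subtypes categorized according to depression and adherence". Data analysis: "The risk of decline of renal function will be estimated for four groups by adherence", crossed with depression and reported as odds ratios with 95% confidence intervals.

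On who is studied, Participants requires "outpatients with type 2 diabetes receiving hypoglycemic medications", and the Discussion gives as its first limitation that "the participants will be patients who regularly visit clinic, causing a risk of bias. This might limit the generalizability of the findings".

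**The concern.** A prescribing record shows that a prescription was written. It does not show that the medication was dispensed or taken. A patient who keeps appointments and is prescribed enough to reach the next one is adherent by this rule, whatever the intake. To score below 80%, a patient must have a substantial part of the year without a prescription, which mostly means missed or delayed visits. Regular attenders are the people least likely to show such gaps.

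The article draws from regular attendance only a limit on generalizability. There is also a problem of internal validity. Depressed patients who attend but do not take their tablets fall into the depression+/adherence+ cell, and the cell meant to represent good adherence then contains some of the people it is compared with. The study could report that adherence makes no difference to renal decline in depressed patients when the measure could not show one. The Discussion promises implications for practitioners and policy makers, so such a null result would carry weight.

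**Working it through.** **1. The plan's own sizing.** Inputs from Sample-size calculations: 165 depressed and 385 non-depressed patients, 18% versus 8% microalbuminuria, 5% level, continuity-corrected chi-square, 88% power. Two-sided, the standard formula gives 166 depressed patients (total about 553), and power at 165/385 is 87.9%. The stated figures reproduce. They cover depression versus no depression only; the section says adherence was left out.

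**2. What the cut-off requires.** 0.80 × 365 = 292 days, and 365 − 292 = 73. A patient is low-adherent only with more than 73 days of the year unprescribed.

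**3. Dilution.** The article gives neither the share of non-takers nor how many of them MPR detects, so both are assumed. Let q be the true share of non-takers among the depressed and Se the fraction that MPR flags, with no taker wrongly flagged. Assume risks of 18% in non-takers and 8% in takers, borrowing the plan's two rates. The risk in the observed adherent cell is then

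[q(1 − Se) × 0.18 + (1 − q) × 0.08] / [q(1 − Se) + (1 − q)].

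For q = 30% and Se = 50%: (0.15 × 0.18 + 0.70 × 0.08) / 0.85 = 0.083 / 0.85 = 9.8%. The observed difference is 18 − 9.8 = 8.2 points. Power is the uncorrected two-proportion normal approximation within the 165 depressed patients.

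| Se (q = 30%) | Observed low cell | Risk difference (points) | Power |
|---|---|---|---|
| 100% | 50 | 10.0 | 47% |
| 50% | 25 | 8.2 | 26% |
| 25% | 12 | 7.6 | 17% |

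For q between 20% and 50%, halving the detection takes power from 42–49% to 22–26%.

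**4. Cell size.** For an assumed share s with MPR below 80%, the low cells hold 165s and 385s patients. The 95% CI for the odds ratio, low versus high adherence among the depressed, is the estimate divided and multiplied by exp(1.96 × SE), where SE² = [1/(165s) + 1/(165(1 − s))] / (0.18 × 0.82), taking 18% in both cells. For s = 10%: SE² = (1/16.5 + 1/148.5) / 0.1476 = 0.456, SE = 0.675, factor 3.8. The power column assumes 18% versus 8% and no misclassification.

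| s | Depressed, low | Non-depressed, low | CI factor | Power |
|---|---|---|---|---|
| 5% | 8 | 19 | 6.2 | 24% |
| 10% | 17 | 39 | 3.8 | 32% |
| 20% | 33 | 77 | 2.7 | 42% |
| 30% | 50 | 116 | 2.4 | 47% |
| 50% | 83 | 193 | 2.2 | 48% |

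The gain beyond s = 20% is modest. Much of the imprecision comes from having 165 depressed patients, and no choice of adherence measure removes it. What MPR adds is the dilution in step 3 and, if s proves low, the upper rows of this table.

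**The case against.** Several points on the other side are sound.

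- **Cell size is unknown.** A reader might infer that the low-adherence cells will be small. The article gives no share below 80%. Its one adherence figure, a mean of 78–82%, would put roughly half below the cut-off if it were an MPR with a symmetric distribution, or about 83 of 165. The article does not say that it is an MPR or that it comes from regular attenders, so it settles the matter neither way.
- **The low cells are not the ones contaminated.** A reader might infer that patients labelled low-adherent are misclassified. The error described here runs mainly the other way: missed non-takers enter the adherent cells.
- **Attendance is not an entry criterion.** Participants asks for current hypoglycemic medication, with no rule on continuity. Regular attendance is a general remark, gaps may arise after entry, and most sites come from a psychiatric network where visits need not coincide with hypoglycemic prescribing. Leftover tablets may also shorten later prescriptions, so MPR need not be wholly blind to non-taking. This makes the misclassification likely rather than certain.
- **Silence on the self-report scales proves little.** Their cut-offs and use may stand in an analysis plan that is not shown. Their absence from the article is not the point raised here. The point is that the one stated rule misclassifies when followed as written.
- **The 18% rate is for microalbuminuria.** Renal function decline is defined on both ACR and eGFR, so the power and interval figures are illustrations and do not forecast the primary outcome.

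**Conclusion.** The point holds as a measurement problem. The stated rule measures continuity of prescribing, and in regular attenders it is likely to class prescribed non-takers as adherent. That contaminates the adherence+ cells and is expected to pull the depression+/adherence− versus depression+/adherence+ contrast toward no difference. Attenuation is the expected direction, not a guaranteed one: it assumes that missed non-takers carry the same risk as detected ones and that few takers are flagged.

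The size cannot be fixed from the article. On the assumed 18% versus 8%, with 30% non-takers of whom half are detected, the difference shrinks from 10 to 8.2 points and power falls from 47% to 26%. Small low-adherence cells are a possibility only. The sample-size arithmetic is not at fault.

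**What to change.** 1. Keep the MPR grouping. Add a second prespecified four-group analysis, reported beside it, that defines low adherence from the self-report data already collected. Prefer the OHA item because it is specific to hypoglycemic medication, with MMAS-8 in support.
2. First reconcile the OHA response scale: the article calls it five-point but lists six options. Then fix the cut-off before outcome data are seen.
3. In the Discussion, state that a prescription-based MPR in regular attenders restricts and misclassifies the exposure, so a null result by MPR alone is not evidence that adherence has no effect.

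A single primary definition combining low MPR or low self-report is not advised. MMAS-8 covers all medication, so it could label patients low-adherent for drugs other than hypoglycemics, and self-report may vary with mood.

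The cost is some wording and one more analysis, with no new data collection. The self-report grouping brings recall and mood-related bias of its own, which is why it should stand beside the MPR grouping and not replace it.
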